### Sensitivity Analyses

#### Exclusion of Workers With Poor Self-Rated Mental Health at Baseline

Workers who redeemed a prescription for psychiatric drugs in the year preceding baseline are excluded from the study. This is done to counteract the possibility of a healthy-worker bias. There is, however, a possibility of residual confounding, since mental health problems may exist also among workers who do not use prescription drugs. We want to know to what extent and in what direction the estimates to be obtained in the primary analysis would change if we were able to exclude all workers with mental health problems at baseline, regardless of whether or not they redeemed prescription drugs in the year preceding baseline. We will address this issue with a sensitivity analysis, which, in addition to excluding the participants who were prescribed medication, also excludes those with poor self-rated mental health at baseline, according to MHI-5 (score ≤ 52). Due to a discrepancy in the response categories of the MHI-5 questions, the sensitivity analysis cannot include data from COPSOQ 2004 and DWECS 2010. In all other respects, we will use the same statistical model as we did in the primary analysis. The parameters will be estimated first with medicine usage only, and then with medicine usage and/or poor self-rated mental health at baseline as exclusion criteria.

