#### Statistical Model

We will use Poisson regression to analyze incidence rates of redeemed prescriptions for psychotropic medicine as a function of weekly working hours (32-40; 41-48; > 48 hours/week). The analysis will be controlled for gender, age (10 year classes), sample (DWECS 1995; DWECS 2000; COPSOQ 2004; DWECS 2005; DANES 2008; and DWECS 2010), shift work (fixed night shifts or rotational shift work schedules vs other), and SES (legislators, senior officials and managers; professionals; technicians and associate professionals; workers in occupations that require skills at a basic level; workers in elementary occupations; and gainfully occupied people with an unknown occupation). With SES we mean socioeconomic status, according to the employment classification module, during the calendar year of the baseline interview. The logarithm of person years at risk will be used as offset. A likelihood ratio test will be used to test the null-hypothesis, which states that the analyzed rates are independent of weekly working hours. The significance level is set to 0.05.

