#### Power Calculations

Based on rates calculated through DNPR in the time period 2001-2005, we expect on average approximately 25 new cases per 1000 person years at risk (PYRS). We expect that the four follow-up periods of nonprevalent cases in the DWECS samples will provide approximately 68,000 PYRS, the five year follow-up of the COPSOQ sample will provide 12,000 PYRS, and the four year follow-up of the DANES sample will provide 16,000 PYRS. Among the ones who worked 32 or more hours per week in 2000 according to DWECS, 26.7% worked more than 40 hours/week and 10.5% worked more than 48 hours/week.

With the above data as input, Figure 1 illustrates the statistical powers to detect contrasts between normal working hours (32-40 hours/week) on one hand and “overtime work” (>40 work hours/week), “moderate overtime work” (41-48 work hours/week), and “very much overtime” (49-100 work hours/week) on the other, as a function of the true rate ratio. If, for example, the true rate ratio between moderate overtime workers and those with normal working hours is 1.2 then we have a 90% chance of detecting the difference; if it is 1.3 then the chance of detection is 99.7%. The power calculations are based on the Poisson distribution, the propagation of error formulas, and the central limit theorem.

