We want to know how and to what extent we can expect our primary analysis to be influenced by uncontrolled differences in the psychosocial work environment. We will address this issue with a sensitivity analysis, where we perform the working hour analysis on the above-mentioned subset of the data, both with and without control for job insecurity and job satisfaction. The following questions will be used: (1) “Are you worried about becoming unemployed?”; (2) “Are you worried about difficulties in finding a new job with your present qualification?”; and (3) “Are you satisfied with your job?”. The questions on job insecurity (which could be answered with either “Yes” or “No”) will be combined into one dichotomous variable. Participants who answered “Yes” to at least one of the two questions will be categorized as having job insecurity, while those who answered “No” to both questions will be categorized as not having job insecurity. Job satisfaction will be treated as a categorical variable in three levels: (1) “To a high degree”; (2) “To some degree”; and (3) “Only to a lesser degree” or “No, or only to a slight degree”. The working time arrangement parameters will be estimated first with, and then without, control for job insecurity and job satisfaction. In all other respects, we will use the statistical model of the primary analysis.

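### The MHI-5 exclusion analysis asks how far and which way the working-hours rate ratio moves, but under a modest association the chance movement between its two nested fits is about as large as, or larger than, the movement sought

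*Protocol article*

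**What the plan says.** Under Sensitivity Analyses, in the subsection on excluding workers with poor self-rated mental health, the protocol article states the question: "We want to know to what extent and in what direction the estimates to be obtained in the primary analysis would change" if every worker with mental health problems at baseline could be left out. Poor mental health means an MHI-5 score of 52 or less.

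The comparison is between two runs, "estimated first with medicine usage only, and then with medicine usage and/or poor self-rated mental health at baseline as exclusion criteria". Both use the surveys with usable MHI-5 items, since "the sensitivity analysis cannot include data from COPSOQ 2004 and DWECS 2010". That leaves DWECS 1995, 2000 and 2005 and DANES 2008. The model is otherwise unchanged: "In all other respects, we will use the same statistical model as we did in the primary analysis".

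The next subsection, on job satisfaction and job insecurity, uses another form of comparison: "The working time arrangement parameters will be estimated first with, and then without, control for job insecurity and job satisfaction". There the factor enters as a covariate and no workers are excluded because of it.

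**The concern.** The quantity of interest is a difference between two rate ratios. The second fit drops the workers with poor MHI-5 and the cases that arise among them. If poor MHI-5 predicts later redemption, those workers carry a larger share of the cases than of the person-years. Removing their cases shifts the estimate by chance even when long hours and poor MHI-5 are unrelated.

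The confidence intervals of the two separate fits do not describe this shift, because the fits share most of their cases. If the chance shift is about the size of the true one, the analysis cannot say reliably whether the primary rate ratio is pulled up or down by unrecorded baseline ill health. That is the question it was written to answer.

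**Working it through.** **Inputs from the protocol (Power Calculations; Follow-Up and Inclusion Criteria; Auxiliary Analysis).** 25 cases per 1000 person-years. 68,000, 12,000 and 16,000 person-years for DWECS, COPSOQ and DANES. 26.7% work more than 40 h and 10.5% more than 48 h, so 16.2% work 41-48 h and 73.3% work 32-40 h. MHI-5 is 52 or less in 7.3% of all employees. OR 1.2 is the size used for the auxiliary power statement.

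**Assumptions, not in the protocol.** Prevalence of poor MHI-5 among non-users, p = 4 to 7.3%. Redemption rate ratio for poor versus better MHI-5, R = 2 to 4. About 15,500 workers. The true OR between long hours and poor MHI-5.

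**1. Reproduce the stated power.** Expected cases: 96,000 x 0.025 = 2,400. For 41-48 h, Var(log RR) = 1/(2,400 x 0.733) + 1/(2,400 x 0.162) = 0.00314, SE 0.056. At RR 1.2, 0.182/0.056 - 1.96 = 1.29, power 90.2%. At RR 1.3 it is 99.7%. Both match the protocol.

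**2. Size of the sensitivity set.** DWECS 2010 supplies 2 of 5+5+5+2 = 17 follow-up years, about 8,000 of the 68,000. The set has 96,000 - 12,000 - 8,000 = 76,000 person-years, or 1,900 cases. SE of log RR in the larger set: 0.063 (41-48 h) and 0.076 (>48 h).

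**3. Chance SD of the change.** For nested sets with equal stratum rate ratios, Var(change) = V x f/(1-f). V is the variance in the larger set and f = pR/(1-p+pR) is the share of cases among the dropped workers. With p = 5.5% and R = 3, f = 0.165/1.110 = 0.149, and SD = 0.063 x sqrt(0.149/0.851) = 0.026. That is a 95% range of about 5% either way on the rate ratio. For >48 h the SD is 0.032.

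**4. Expected change.** log[(1+p1(R-1))/(1+p0(R-1))]. With p0 = 5.5% and OR 1.2, p1 = 6.53%, giving log(1.1306/1.1100) = 0.018. This is 0.018/0.026 = 0.70 SD, so the direction is wrong with probability 24%.

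**5. Range at OR 1.2, by formula.**

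| p, R | Expected change | SD, 41-48 h | SD, >48 h |
|---|---|---|---|
| 4%, 2 | 0.007 | 0.018 | 0.022 |
| 5.5%, 3 | 0.018 | 0.026 | 0.032 |
| 7.3%, 4 | 0.032 | 0.035 | 0.043 |

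Simulation gives slightly larger SDs. It lets the number of dropped workers vary and places more of them among those with long hours. Over these ranges the SD is about 0.02 to 0.05, the expected change 0.007 to 0.033, and the direction is wrong in 23 to 39% of runs.

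**6. Stronger associations.** For 41-48 h the expected change is 1.0 to 2.2 SD at OR 1.5 and 1.9 to 4.1 SD at OR 2.0. Over both hours groups the simulated direction is wrong in 3 to 26% and 0 to 12% of runs.

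**7. Same workers, MHI-5 as a covariate.** No cases are lost, so the noise comes mainly from chance imbalance in poor MHI-5 between hours groups. For p = 5.5% and R = 3, with 15,500 x 0.162 = 2,511 and 15,500 x 0.733 = 11,362 workers, SD is about (2/1.11) x sqrt(0.055 x 0.945 x (1/2,511 + 1/11,362)) = 0.009. Simulation at OR 1.2 gives 0.010 (0.012 for >48 h), the same expected change of 0.018, and the wrong direction in 3% and 6% of runs. Over the full ranges the SD is about a quarter to two-fifths of that for exclusion, with the wrong direction in 1 to 9%.

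**The case against.** **An unstated interval is reporting detail.** An article may leave it to a fuller plan. This stands, and the missing interval alone would not be a finding. The point rests on the comparison that the article does fix, and on how it fits the question the article asks.

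**A reader might infer that two separate samples are compared, or that noise swamps the result whatever the truth.** The protocol supports neither. The second set is a subset of the first, both come from the same four surveys, and the SD of the change (about 0.03) is roughly half the SE of the rate ratio itself (0.063). A strong association would usually be visible. Nor does the protocol say that it will draw a conclusion from two bare point estimates.

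**OR 1.2 is not an expected value.** In the auxiliary analysis it is a detectable effect, in a population that includes medicine users. R and the prevalence among non-users are also assumed. This stands, and the result is conditional on the ranges shown.

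**A true shift of 1 or 2% changes no conclusion.** This is largely fair for the true shift. But a chance movement of about 4 to 7% for 41-48 h is what would be seen, and it could be taken for residual confounding or could hide it.

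**Restriction answers the stated question directly, and adjustment answers another.** The two agree only if the hours rate ratio is equal in both MHI-5 strata. That is a reason to keep the exclusion analysis and add to it.

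**Conclusion.** The concern holds in a limited form. If poor MHI-5 is modestly associated with long hours (OR about 1.2), with R = 2 to 4 and p = 4 to 7.3%, the chance SD of the change is as large as or larger than the expected change. The direction would then be wrong in roughly a quarter to two-fifths of studies. The analysis can still reveal a strong association. Primary hypothesis testing is not touched. This is an inexpensive improvement to a sensitivity analysis and does not invalidate the plan. None of these calculations covers the job satisfaction and job insecurity comparison, so no defect is claimed there.

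**What to change.** In the subsection on excluding workers with poor self-rated mental health:

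1. Keep the exclusion analysis as written.
2. Add the primary model fitted with and without the indicator for MHI-5 of 52 or less as a covariate, in the same DWECS 1995, 2000, 2005 and DANES 2008 workers.
3. For both versions, report the ratio of the two rate ratios for 41-48 h and for >48 h, with a 95% CI from a bootstrap that resamples persons.
4. Describe a direction of change only in light of that CI.

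The cost is a few lines of text and one bootstrap on data already held. The covariate version's precision depends on equal hours rate ratios across MHI-5 strata, so state that assumption and show both versions side by side. Giving the same interval for the job satisfaction and job insecurity comparison is optional.

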#### Are the Estimates Influenced By Job Satisfaction and Job Insecurity?

It has been shown that the psychosocial work environment is associated with mental health. According to a meta-analytic review by Stansfeld and Candy, common mental disorders were predicted by job strain, low decision latitude, low social support, high psychological demands, effort-reward imbalance, and high job insecurity [42]. Another finding, of particular interest to the present study, is a statistically significant relation between baseline job dissatisfaction and subsequent usage of psychiatric prescription drugs in a recent sample of 40-60 year old employees of the City of Helsinki [43].

Job satisfaction does not measure the work environment directly. It has, however, been shown to be highly dependent on the psychosocial work environment. The COPSOQ scales on demands, influence and development, interpersonal relations, and leadership explained 59% of the variation in job satisfaction, in a sample of employees in Germany 2004 [44]. Further, a meta-analysis based on 485 studies suggested that job satisfaction, with an overall correlation of 0.37 across four health outcomes, was an important factor influencing the health of workers [45].

Unfortunately, the questions and response categories that deal with psychosocial dimensions differ between our questionnaires to a degree that make it impossible to obtain any psychosocial measure that stays the same in all of the datasets. The questions and response categories for job satisfaction and job insecurity remained, however, unchanged throughout the questionnaires of DWECS 1995, 2000, and 2005, and this subset of the data is large enough to make a sensitivity analysis meaningful.

We want to know how and to what extent we can expect our primary analysis to be influenced by uncontrolled differences in the psychosocial work environment. We will address this issue with a sensitivity analysis, where we perform the working hour analysis on the above-mentioned subset of the data, both with and without control for job insecurity and job satisfaction. The following questions will be used: (1) “Are you worried about becoming unemployed?”; (2) “Are you worried about difficulties in finding a new job with your present qualification?”; and (3) “Are you satisfied with your job?”. The questions on job insecurity (which could be answered with either “Yes” or “No”) will be combined into one dichotomous variable. Participants who answered “Yes” to at least one of the two questions will be categorized as having job insecurity, while those who answered “No” to both questions will be categorized as not having job insecurity. Job satisfaction will be treated as a categorical variable in three levels: (1) “To a high degree”; (2) “To some degree”; and (3) “Only to a lesser degree” or “No, or only to a slight degree”. The working time arrangement parameters will be estimated first with, and then without, control for job insecurity and job satisfaction. In all other respects, we will use the statistical model of the primary analysis.

### Shift Work

#### The Effect of Shift Work on Health

We control for shift work in the primary, the auxiliary, and all of the secondary analyses. In doing so, we will automatically obtain parameter estimates that can be used to calculate rate ratios for psychotropic medicine as a function of shift work (fixed night shifts or rotational shift work schedules vs other). To our knowledge, the prospective relationship between shift work and psychotropic medicine has never been studied in a general working population. Hence, the effect of shift work will be of interest, not only as a control variable, but also as a potential contribution to the body of knowledge on “shift work and health”. In our opinion, the data material, inclusion criteria, significance levels, and statistical models that we use to estimate effects of long working hours are appropriate also for the estimation of shift work effects. Moreover, the primary statistical power is sufficient and the exposure is stable enough to make such an effort worth the while (see below). We will therefore publish results on shift work in addition to the ones on long working hours.

#### Transitions Between Work-Schedule Categories

We used DWECS data to cross-tabulate an employee’s work schedule category in 2000 with that in 2005. We included all who were economically active and 30 years or older in both waves. More than half (55.1%) (113/205) of the workers with shift work and 90.90% (1858/2044) of the workers with nonshifting work hours in 2005 had the same type of work schedule five years earlier, while 37.8% (113/299) of the workers with shift work and 95.28% (1858/1950) of the workers with nonshifting work hours in 2000 had the same type of work schedule five years later. Cohen’s kappa for agreement between the work schedule category in 2000 and in 2005 was 0.38 (95% CI 0.32-0.44), which indicates fair agreement according to Landis and Koch [36].

#### Power Calculations for the Shift Work Hypothesis

According to DWECS 2000, 14.4% of the ones who worked 32 or more hours per week were either on fixed night shifts or rotational shift work schedules. We applied this information to the data and assumptions we used in the power calculation for the primary analysis and calculated the statistical power to detect a contrast between fixed night shifts or rotational shift work schedules on one hand, and nonshifting nonnight work on the other (Figure 2 shows this contrast).

**Figure 2 figure2:**
[figure not shown]
Power of detecting differences in psychiatric morbidity rates in Denmark, between employees on fixed night shifts or rotational shift work schedules and employees with other work schedules, as a function of the true rate ratio.

## Results

The publication of the present study protocol ends the design phase of the project. In the next phase, the questionnaire data will be forwarded to Statistics Denmark where they will be linked to data on deaths, migrations, socioeconomic status, and redeemed prescriptions for psychotropic medication. We expect the analysis to be completed by the end of 2014 and the results to be published mid 2015.

## Discussion

### The Research Project

This protocol gives a detailed plan for a research project aimed at investigating the possibility of a prospective association between weekly working hours and use of psychotropic medication in the general working population of Denmark. We have shown that the statistical power is sufficient, and that the exposure is stable enough to make the study worth the while. We have also designed an auxiliary study, which will help us to interpret the results of the primary analysis, which, a priori, might be affected both by differences in morbidity and differences in propensity to seek treatment.

The presented study will utilize the work hour categories proposed by Kleppa et al [19], that is, 32-40 to represent normal weekly working hours, 41-48 to represent overtime work which lies within the limits of the European working time directive, and 49-100 to represent overtime work beyond the threshold of the directive. These cut-off points will enable us to evaluate the results from a societal (national burden of disease) perspective, since they allow us to answer the following questions, “Are there important differences between the average rate among people with normal working hours, and that among people with overtime work within and beyond the EU directive, respectively?”. The span of the maximum work hour category complicates, however, the interpretation of the results from an individual perspective. A null finding, which would indicate that the effect is unimportant from a societal perspective, does not necessarily mean that it is safe to work, for example, 60 hours or more per week. From this viewpoint, we understand that an extra work hour category would be of interest, especially to people in nations where it is normal to work 50 hours (or more) per week. An extra category would, however, reduce the statistical power of the analysis, and we prefer to have one sufficiently powered category (> 48 hours), instead of two underpowered categories (eg, 49-59; ≥ 60 hours).

Since our goal is to obtain statistical certainty, we choose to base our primary case definition on the aggregate of all types of psychotropic medicine, rather than performing analyses on particular types. It makes sense to do so. Anxiety disorders are strongly and positively correlated with depressive disorders [19,22], and sleeping disorders are strongly and positively correlated with both anxiety and depressive disorders [46]. Based on a linkage between the ECM and the National Prescription Registry, 95.83% (75,815/79,117) of all new cases of psychotropic medicine use among employees in Denmark in 2001 concerned a drug in the category anxiolytics (33.26%, 26,315/79,117, of all cases), antidepressants (30.50%, 24,131/79,117, of all cases), or hypnotics and sedatives (32.07%, 25,369/79,117, of all cases).

It also makes sense to control for gender, age, socioeconomic status, and shift work. It is well established that women are treated for depression [47], anxiety [48,49], and insomnia [50] more often than men and that the occurrence of these diagnoses varies with age [47,49,50]. It is also well established that socioeconomic status is negatively correlated with mental illness; the lower the SES, the higher the rate of illness [51]. Shift work may induce the so-called shift work sleep disorder, and it is possible that such a condition will be treated with hypnotics as well as wakefulness-promoting drugs [52].

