**Conclusions:**

The proposed project will be free from hindsight bias, since all hypotheses and statistical models are completely defined, peer-reviewed, and published before we link the exposure data to the outcome data. The results of the project will indicate to what extent and in what direction the national burden of mental ill health in Denmark has been influenced by long working hours.

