### The Danish Government and Increased Working Hours

The Danish government wants to increase the total number of work hours in the nation by: (1) decreasing the number of hours that are lost due to sickness absence and early retirement, and (2) encouraging the ones that are working, to work longer hours [18]. From this perspective, we want to know if there is a positive, negative, or no correlation between long working hours and incidence of psychiatric disorders in the Danish working population, in other words, if pathogenic effects of long working hours outweighs the salutogenic effects or vice versa. We are especially interested in the situation among the people who perform moderate overtime work (41-48 work hours/week), that is, overtime work which lies within the limits of the European working time directive. If there is a nonnegligible correlation between long working hours and subsequent mental ill health, then this needs to be taken into account in the planning and evaluation of strategies aimed at getting more people to work extra hours.

The existing literature does not provide the information we need to settle this question.

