### Aim and Hypothesis

The null-hypothesis of the present project is that long working hours, to the extent that it is currently practiced in Denmark, neither adds to nor subtracts from the national burden of mental ill health.

The project aims at testing the above hypothesis in a prospective cohort study on a random sample of the Danish working population. The null-hypothesis will be rejected if subsequent rates of mental ill health (manifested by the use of psychotropic medicine) among people with long working hours at baseline differ significantly from those among people with normal working hours. The analysis will be adjusted for gender, age, socioeconomic status, and shift work. It will only include those who are free from symptoms at baseline.

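### A non-significant primary test is read as showing a societally unimportant effect, with no margin or interval to support that reading

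*Protocol article*

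**What the plan says.** Under The Research Project in the Discussion, the protocol explains why its three working-hour categories suit a national-burden question. It then writes of "A null finding, which would indicate that the effect is unimportant from a societal perspective". The same sentence warns that such a result need not make very long weeks safe for an individual. The societal reading carries no such caution.

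Under Aim and Hypothesis, the null is that long working hours "neither adds to nor subtracts from the national burden of mental ill health", to be rejected if rates differ significantly. Under Statistical Model, rates are modelled "as a function of weekly working hours (32-40; 41-48; > 48 hours/week"), and "A likelihood ratio test will be used to test the null-hypothesis, which states that the analyzed rates are independent of weekly working hours". The level of that test is fixed in one further sentence: "The significance level is set to 0.05".

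The Introduction ties the result to policy with the words "If there is a nonnegligible correlation between long working hours and subsequent mental ill health", but gives no size for that adjective. The abstract, for its part, says: "The results of the project will indicate to what extent and in what direction the national burden of mental ill health" is affected by overtime.

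**The concern.** A test of no difference can reject the null or fail to reject it. Failing to reject shows that the effect is small only if the confidence interval excludes every effect that would matter, and that requires a stated smallest effect that matters. The protocol gives neither a margin nor an interval criterion, yet it says in advance what a null result would mean for society.

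The project is meant to inform a government policy of encouraging longer hours, and its credibility rests on fixing everything before linkage. A reading published in advance carries that same authority, so a non-significant result could be reported as reassurance while the data remain compatible with a relevant excess.

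**Working it through.** **Inputs (Power Calculations).** The expected rate is "approximately 25 new cases per 1000 person years at risk (PYRS"). Person-years are 68,000 + 12,000 + 16,000 = 96,000, so cases are 96,000 × 0.025 = 2,400. In DWECS 2000, 26.7% of those working 32 h or more exceeded 40 h and 10.5% exceeded 48 h. The shares are therefore 73.3% (32-40 h), 16.2% (41-48 h) and 10.5% (>48 h). The test is two-sided at 0.05.

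**Step 1: reproduce the stated power.** Compare 41-48 h with 32-40 h at a true rate ratio of 1.2, holding the average rate in these two groups at 0.025.
- Person-years: 96,000 × 0.733 = 70,368 and 96,000 × 0.162 = 15,552. Cases: 85,920 × 0.025 = 2,148.
- Rates: 2,148/(70,368 + 1.2 × 15,552) = 0.02413, and 1.2 times this = 0.02895.
- SE of the difference: √(0.02413/70,368 + 0.02895/15,552) = 0.001485. Then z = 0.00483/0.001485 = 3.25 and power = Φ(3.25 − 1.96) = 90%.
- The same steps at 1.3 give z = 4.67 and 99.7%.

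Both stated figures reproduce, so the inputs are read as the authors used them.

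**Step 2: power of the planned primary test.** Three categories give 2 degrees of freedom and a critical value of 5.99. The noncentrality is 2 Σ μ ln(μ/μ₀), where μ₀ is the expected number of cases under no effect and μ the number under the alternative, with the total held at 2,400.

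For a rate ratio of 1.10 in both overtime categories, μ₀ = 1,759.2 / 388.8 / 252.0 and μ = 1,713.5 / 416.6 / 270.0. The noncentrality is 4.39 and power is 45%. A simulation of 200,000 studies gave 45.0%. If 25 per 1000 is instead the reference-group rate, power is 46%.

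| True rate ratio, 41-48 h / >48 h | Power, 2-df test |
|---|---|
| 1.10 / 1.10 | 45% |
| 1.10 / 1.00 | 33% |
| 1.00 / 1.10 | 24% |
| 1.00 / 1.20 | 73% |
| 1.15 / 1.15 | 80% |
| 1.20 / 1.20 | 96% |

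For comparison, a pooled 1-df likelihood ratio contrast (>40 h against 32-40 h) at 1.10 has the same noncentrality, 4.39, and 55% power. Across other test forms its power is 52-57%.

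**Step 3: what a null result could exclude.** At an estimated rate ratio of exactly 1, SE(log RR) = √(1/1,759.2 + 1/388.8) = 0.0560 for 41-48 h and √(1/1,759.2 + 1/252.0) = 0.0674 for >48 h. The 95% limits are exp(±1.96 × SE): 0.90 to 1.12 and 0.88 to 1.14. Pooled overtime gives 0.91 to 1.09.

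At the edge of non-significance, with one category carrying the whole effect, the largest estimate that the 2-df test fails to reject is about 1.14 (41-48 h) or 1.17 (>48 h). The upper 95% limits are then about 1.27 and 1.32. A non-significant result can therefore coexist with the 1.2 and 1.3 that the protocol itself uses to illustrate power.

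**The case against.** Much can be said for the authors. The clause is a subordinate remark in a Discussion sentence whose purpose is caution. The plan has no formal rule for accepting the null, and Secondary Analyses treats later results as exploratory when the null is not rejected. The preceding sentence asks about important differences, which is a question of size. The 10% excess used above is an illustration chosen for this review, not a threshold in the protocol. All of this stands and lowers the severity. It does not rescue the inference, because the clause still says what a null finding would indicate and nothing in the article supplies the criterion.

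Three stronger readings are tempting, and the documents do not support them.
- A reader might infer that the design misses a 10% excess in all overtime workers more often than not. That holds only for the 2-df test, by a narrow margin (about 55% missed). The pooled contrast, one of the three for which the protocol reports power, detects it slightly more often than not.
- A reader might infer that a null result would be uninformative. It would not be: power is 80% at 1.15 and 96% at 1.20 in both categories, and estimates near 1 would exclude sizeable effects.
- A reader might infer that the plan is defective because it estimates no attributable fraction. A journal article may leave derived summaries to a fuller plan. Attributable cases would also sit uneasily with the protocol's own cautions on causality and prescription bias.

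**Conclusion.** The concern holds as a point of interpretation, at moderate severity. The protocol links a null finding to societal unimportance without a margin or an interval criterion, and its planned test leaves modest excesses, or excesses confined to one category, undetected with substantial probability: 55% missed at 1.10 in both categories and 27% missed at 1.20 in >48 h only.

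These figures assume 2,400 cases, the DWECS 2000 exposure shares in every sample, and no loss of precision from covariate adjustment, which would usually lower power somewhat. The core point depends on none of them. The exposure categories, endpoint, model and test are not in question.

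**What to change.** Delete the clause, or reword it to say that a non-significant test does not by itself show that the effect is unimportant.

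Before linkage, state the rate-ratio margin that the investigators regard as negligible. Call the effect societally unimportant only if the 95% confidence intervals of both rate ratios (41-48 h and >48 h, each against 32-40 h) lie wholly inside it. Otherwise report a non-significant test as inconclusive. The margin must be set before linkage, because one chosen afterwards would lose the protection from hindsight bias that the protocol claims. An attributable fraction is optional.

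The cost is one paragraph of wording, with no new data and no change to the model or test. The downside is that some null results become inconclusive. On the figures above, an upper margin below about 1.14 could not be met for >48 h even if the estimate were exactly 1, and the investigators should know this when they choose it.
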